## Abstract

**Background:**

Weight loss interventions have not been advocated for overweight/obese older adults due to potential loss of skeletal muscle and strength impacting on physical function with potential loss of independence. Carotenoids and polyphenols are inversely associated with sarcopenic symptomology. This paper reports the protocol of a study evaluating the efficacy of a high-protein, energy restricted diet rich in carotenoids and polyphenols on body composition, muscle strength, physical performance and quality of life in overweight and obese older adults.

**Methods:**

This randomised controlled clinical trial will recruit community-dwelling, healthy overweight and obese older adults (≥60 years) for a 12-week weight loss intervention. Seventy-three participants will be recruited and randomized to an energy restricted (~30% restriction), isocaloric diet (30% protein; 30% carbohydrate; 40% fat) enriched with either: a) 375 g/d of high carotenoid vegetables, 300 g/d high carotenoid fruit, and 40-60 ml extra-virgin olive oil (EVOO); or b) 375 g/d of lower carotenoid vegetables, 300 g/d lower carotenoid fruit, and 40-60 ml Polyunsaturated fatty acid (PUFA) based oil. All participants will receive individual dietary counselling each fortnight for the duration of the study and will be asked to maintain their habitual level of physical activity throughout the study. The primary outcome will be appendicular skeletal muscle (ASM) assessed by dual energy X-ray absorptiometry (DXA). Secondary outcomes will include body weight, fat-free mass (FFM), fat mass (FM), muscle strength (Isometric hand-grip strength), physical performance (Short Physical Performance Battery), physical activity (International Physical Activity Questionnaire) and health related quality of life (SF-36). Outcomes will be measured at baseline and at week 12.

**Discussion:**

The results of this study will provide a novel insight relating to the potential influence of high carotenoid and polyphenol intakes on attenuation of ASM during dietary energy-restricted weight loss in overweight and obese older adults.

**Trial registration:**

The trial was registered on the Australia New Zealand Clinical Trials Register (ACTRN12616001400459); Trial registration date: 10th October, 2016.

## Background

Global trends in population ageing are pronounced and historically unprecedented leading to an increased need to promote healthy ageing. It is estimated that approximately one-quarter of the population in the United Kingdom (UK), Australia and in the United States (US) will be aged 65 years and older by 2050 [1, 2]. A major concern for an ageing population is potential loss of independence, institutionalisation and disability due to an age-related decline in skeletal muscle mass (SMM) and function and/or sarcopenia [3, 4].

Ageing is associated with changes in body composition that typically results in a reduction in muscle size and quality, and concomitant accumulation of fat mass (FM) [5]. The coexistence of diminished muscle mass coupled with reduced physical performance such as gait speed and/or muscle strength in addition with excessive adiposity has been termed ‘sarcopenic obesity’ [6]; this has important functional implications for older adults as there is a growing body of literature suggesting that sarcopenic obesity exacerbates age related decline in physical function which promotes frailty, physical inactivity, impairs quality of life and loss of independence [7, 8]. As a result of the rising prevalence of obesity in older adults, there are suggestions that the most common phenotype of frailty in the future may be an obese, disabled older person [9]. Therefore, effective interventions are required to facilitate improved health outcomes and enhance the quality of life of overweight and obese older adults.

The presentation of overweight and obesity in older adults presents a complex challenge to healthcare professionals for the prescription of appropriate interventions. In particular, a conundrum is the negative consequences of energy restricted diets on the loss of SMM, bone mineral content and muscle strength [10]. On average, approximately 25% of body mass lost by dietary energy restriction consists of fat-free mass (FFM) [10–12]. Due to the potential exacerbation of sarcopenic symptomology and functional decline, weight loss has not traditionally been recommended for obese older adults [13]. The addition of resistance training to an energy restricted diet has previously been shown to attenuate the loss of skeletal muscle, increase muscle strength and ameliorate frailty in obese older adults relative to either intervention alone [14–16]. However, a subset of obese older adults are limited in their capacity to engage in physical activity due to excess adiposity, reduced muscle strength and functional impairment [17]. Moreover, individuals with functional disability are unlikely to participate in physical activity at an intensity sufficient to induce a negative energy balance or to fully preserve lean tissue mass [18]. Therefore, novel dietary strategies to preserve SMM and strength during energy intake restriction are warranted.

Manipulating dietary composition during energy intake restriction, in particular protein intake, may attenuate the loss of SMM and strength. To date, most geriatric obesity weight loss trials have adopted dietary strategies involving the manipulation of dietary protein to preserve lean tissue during energy intake restriction [19–26]. Dietary protein intake stimulates muscle protein synthesis (MPS) and facilitates postprandial muscle protein accretion [27, 28]. Despite earlier studies suggesting that a decline in basal MPS may contribute to skeletal muscle wasting in the elderly [29, 30]; it appears that the elderly may be less able to efficiently utilize amino acids for MPS, resulting in a blunted muscle protein synthetic response to an anabolic stimuli, a phenomenon termed anabolic resistance [27, 31]. As of consequence, evidence based recommendations for protein intake in older adults have recently been published [32, 33]. However, there are no specific recommendations for obese older adults during energy intake restriction. Weijs and Wolfe [20] recently showed that at least 1.2 g/kg body weight or 1.9 g/kg FFM as optimal daily protein intake for obese older adults during energy intake restriction. Despite this however, an important determinant of MPS is not only an adequate intake of dietary protein. Plasma levels of antioxidants, in particular carotenoids and polyphenols, have shown to be inversely associated with sarcopenic symptomology and frailty [34–38]. Similar observations have been observed for fruit and vegetable intake [39–42]. Furthermore, a number of observational studies have reported that greater adherence to a Mediterranean Diet, characterized by a high intake of carotenoids from fruits and vegetables and polyphenols from extra-virgin olive oil (EVOO), is associated with lower odds of sarcopenia, frailty and improved mobility and physical performance [43–51]. Vegetable intake, in particular green-leafy vegetables, has shown to be associated with increased levels of physical activity [52]. In addition, increases in plasma lutein through supplementation are correlated with increases in physical activity and reductions in sedentary time in older adults [53]. Thus, an increase in carotenoids may attenuate loss of SMM by increasing physical activity during dietary energy restriction. The efficacy of carotenoid rich fruits and vegetables plus EVOO when coupled with a high protein, energy restricted diet however is unknown.

The aim of this study is to investigate the effect of a high protein diet rich in carotenoids from fruits and vegetables and polyphenols from EVOO on appendicular skeletal muscle (ASM) in overweight and obese older adults during dietary energy-restricted weight loss. Secondary outcomes included: body weight, FFM, fat mass (FM), muscle strength, physical performance and health related quality of life. The current paper presents the protocol for the recruitment and randomisation, study design, dietary intervention and key outcome assessments.

## Methods

### Study design, participants and recruitment

This is intended to be a 12-week randomised controlled trial (RCT) involving overweight and obese older adults aged ≥60 years. Community dwelling healthy older adults will be recruited from the Sunshine Coast region, Queensland, Australia via local flyers, newspaper advertisements and social media. Participants who express interest will be screened over the telephone by research personnel against eligibility criteria, outlined in Table 1. Body mass index (BMI) is one of the more common methods used to assess obesity in primary care and in subspecialty settings. Considering the recent evidence related to all-cause mortality risk and BMI in older adults [54], participants will be eligible to participate in the study based on a BMI classification of ≥27 kg/m^2^, consistent with previous geriatric obesity reduction trials [19–23].

**Table 1 Tab1:** Participant eligibility criteria

Inclusion Criteria	Exclusion Criteria
Aged ≥60 years	Poor cognition/unable to follow study protocol/unable to provide informed consent
Community-dwelling	Type 2 diabetes mellitus
Overweight or obese (BMI: ≥27 kg/m^2^)	Liver disease, unstable cardiovascular disease, respiratory, neurological or gastrointestinal diseases
	Malignancy
	Current or recent use of anti-inflammatory drugs, corticosteroid agents or sex steroid compounds
	No current involvement in a secondary study at the time of enrolment

*Abbreviations: BMI* Body Mass Index

Eligible participants will be provided with detailed study information and consent form via post or email, and scheduled to attend a baseline appointment upon providing study consent. At the baseline appointment, body mass, height and BMI will be measured to confirm eligibility. Participants will be recruited via rolling recruitment and randomly allocated to a 12-week prescribed and individualized energy restricted diet enriched with high carotenoid fruits and vegetables and EVOO; or, a 12-week prescribed and individualized energy restricted diet enriched with lower carotenoid fruits and vegetables and a polyunsaturated fatty acid (PUFA) based oil. Volunteers will be randomly assigned to either group following the completion of all baseline measurements. Allocation will be stratified by BMI (27–29.9 kg/m^2^; ≥30 kg/m^2^) using a random number, computer generated randomisation schedule generated and managed by a member of the research team. An overview of the recruitment method and randomisation process is provided in Fig. 1.

**Fig. 1 Fig1:**
[figure not shown]
Flow diagram for study participants

All participants will attend the weight management clinic at the University of the Sunshine Coast at baseline and every fortnight for the duration of the study. This study will be conducted according to the guidelines laid down in the Declaration of Helsinki and all procedures involving human participants have been approved by the Human Research Ethics Committee (A/16/801), University of the Sunshine Coast, Queensland, Australia. This trial has been registered with the Australian and New Zealand Clinical Trials Registry (reg no: ACTRN12616001400459). Written informed consent will be obtained from all participants before commencement.

### Data collection

The timeframe for this study will be 18 months, from 1 July 2016 to 30 April 2018. This timeframe includes the collection of all outcome measures and statistical analysis pertaining to this study**.** Assessment of all outcome measures (primary or secondary) will be conducted at baseline and Week 12. The primary outcome measure for this study will be ASM. Secondary outcomes will include body weight, FFM, FM, muscle strength, physical performance, physical activity and health related quality of life. Participants will also report to the clinic each fortnight for the duration of the study where they will be weighed and receive individual dietary counselling by an Accredited Practising Dietitian (APD).

In preparation for all outcome assessments, participants will present to the clinic after an overnight fast wearing light figure hugging clothing without metal zips, tags, or studs. Following the completion of all baseline assessments, participants will be provided with a 3-day food diary and commence a one-week ‘run-in’ period before beginning the 12-week intervention. During the ‘run-in’ week, participants will be instructed to consume their habitual dietary intake. Throughout this period, participants will be asked to record all food and fluid intake across three days (two consecutive weekdays and one weekend day). Upon completion of the ‘run-in’ week, participants will return to the weight management clinic (Week 0) where food diaries will be verbally cross-checked for completeness by an APD, and any ambiguities will be clarified. Participants will be re-weighed following completion of the ‘run-in’ week.

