^a^Depending on their allocation, participants will be asked to consume fruits and vegetables from the allocated list only

^b^Participants randomized to the high carotenoid plus EVOO group will be asked to consume 375 g/d of high carotenoid vegetables and 300 g/d high carotenoid fruit

^c^Participants randomised to the lower carotenoid plus PUFA oil group will be asked to consume 375 g/d of lower carotenoid vegetables and 300 g/d lower carotenoid fruit

All participants will receive individual dietary counselling by an APD and will be provided detailed instructions on how to maintain and record their daily dietary checklist. If any deviations are made from the prescribed quantities in the checklist, participants will be instructed to record this. All participants will be provided with a selection of recipes, reflecting the composition of the dietary protocol. In addition, all participants will be provided a list outlining the type and variety of fruits and vegetables required for consumption. If participants request mid-meal snacks between meals, they will be counselled on selecting high protein based options. Volunteers will return the checklists every fortnight and these will be discussed with the APD to clarify serving sizes and address any potential issues or problems with compliance toward the dietary protocol. As an additional measure of adherence to the dietary protocol, body weight will be recorded each fortnight for the duration of the study. All participants will be asked to maintain their habitual level of physical activity for the duration of the study. All individual consultations will last between 20 and 30 min in duration. To facilitate compliance, all participants will be provided with a sample fruit and vegetable hamper valued at $30AUD each fortnight for the duration of the study, reflecting the key fruits and vegetables specific to their group allocation. Participants randomized to the high-carotenoid fruits and vegetables, plus EVOO group will also receive EVOO for the duration of the study. All other food(s) prescribed in the energy restricted diet will be provided by the participant.

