### Power calculations, intention to treat and statistical analyses

This study was powered on the primary outcome of change in ASM. Based on data from a previous intervention assessing preservation of ASM during intentional weight loss in obese older adults [22] it was estimated that *n* = 56 participants would provide 80% power to detect a significant (*P* < 0.05, 2-sided) change in ASM between the two study groups of 0.9 kg ± 1.2 kg. Assuming an attrition rate of 30%, the target sample size will be *n* = 73 participants. All analyses in the proposed study will be performed using intention-to-treat analysis, with all randomised participants included in the final analysis irrespective of compliance.

Non–normally distributed variables will be logarithmically transformed before analysis. Where normality is not achieved, non-parametric methods for analyses will be used. Descriptive statistics will be presented for baseline characteristics, and independent sample t-tests or chi square analysis will be used to ensure that there are no significant differences between randomised groups. Paired t-tests will be used to identify whether outcome parameters change over time. After screening for assumptions related to multicollinearity, normality, linearity, homogeneity and reliability of covariates, analysis of covariance (ANCOVA) will be applied to identify differences between groups over time, with diet groups as the independent variable and outcome parameters as the dependent variable. Covariates will be determined using a correlation matrix to identify significant interactions between potential confounders. Analyses will be performed using SPSS for Windows 24.0 software (SPSS Inc., Chicago, IL, USA) with statistical significance set at *P* < 0.05.

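### Body weight is recorded every fortnight, but its outcome is fixed at baseline and Week 12, so leavers' on-study weights have no stated place in the analysis

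*Protocol article*

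**What the plan says.** Under Data collection, the Protocol article fixes the timing of every outcome: "Assessment of all outcome measures (primary or secondary) will be conducted at baseline and Week 12". Body weight is among them: "Secondary outcomes will include body weight, FFM, FM, muscle strength, physical performance, physical activity and health related quality of life". The same section then provides for more frequent weighing: "Participants will also report to the clinic each fortnight for the duration of the study where they will be weighed". It also has participants re-weighed at Week 0, after the one-week run-in.

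Under Dietary protocol, the fortnightly weights are given a purpose: "As an additional measure of adherence to the dietary protocol, body weight will be recorded each fortnight for the duration of the study". No other use is stated.

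Under Power calculations, intention to treat and statistical analyses:
- Attrition: "Assuming an attrition rate of 30%, the target sample size will be" 73.
- Analysis set: intention to treat, "with all randomised participants included in the final analysis irrespective of compliance".
- Within-group change: "Paired t-tests will be used to identify whether outcome parameters change over time".
- Between-group comparison: "analysis of covariance (ANCOVA) will be applied to identify differences between groups over time".

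The article does not say how a missing Week 12 weight is handled, or whether any interim weight enters the body-weight analysis.

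**The concern.** Body weight differs from the other outcomes. For DXA, grip strength, physical performance and the questionnaires, a participant who leaves has no on-study measurement, so two time points are all there is. For body weight, a leaver may have up to five on-diet weighings (weeks 2, 4, 6, 8 and 10). Someone who leaves after the week 8 visit has four. A paired t-test or ANCOVA on baseline and Week 12 takes none of them.

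Two things are at stake. First, if people who leave a weight-loss diet tend to be those losing least, a result based on Week 12 attenders describes the more successful participants. Second, the aim is preservation of ASM during weight loss, so whether the two diets produced similar weight loss is needed to interpret the primary comparison.

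**Working it through.** **Inputs from the Protocol article**
- 73 to be randomised, 56 evaluable, 30% attrition (Power calculations section).
- Target loss of about 0.5 to 1.0 kg per week (Dietary protocol). Over 12 weeks: 12 × 0.5 = 6 kg to 12 × 1.0 = 12 kg.

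**The plan's own figure.** 56 × 1.30 = 72.8, which rounds to the stated 73. This sample size rests on ASM; the article gives no figure for body weight.

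**Expected leavers.** 0.30 × 73 = 21.9, about 22. Remaining: 0.70 × 73 = 51.1, about 51.

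**Mean loss from Week 12 attenders only.** Let C be the mean Week 12 loss of completers, f the fraction of C that leavers would have lost at Week 12, and d the attrition. The mean over everyone randomised is (1 − d)C + dfC. The overstatement is therefore

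C − [(1 − d)C + dfC] = dC(1 − f).

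The documents give no value for f, so a range is assumed, with d = 0.30:

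| f | C = 6 kg | C = 12 kg |
|---|---|---|
| 0 | 0.30 × 6 × 1 = 1.8 kg | 0.30 × 12 × 1 = 3.6 kg |
| 0.5 | 0.30 × 6 × 0.5 = 0.9 kg | 0.30 × 12 × 0.5 = 1.8 kg |
| 1 | 0 | 0 |
| 1.1 | −0.18 kg | −0.36 kg |

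The sign depends on f. There is overstatement only if leavers lose less than completers, and slight understatement if they lose more.

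**Difference between diets.** Take the same C in both arms.
- Same attrition and same f in both arms: the two biases cancel and the difference is unbiased.
- Same f, attrition d₁ and d₂: size of bias = C(1 − f)|d₂ − d₁|. With 25% v 35% (assumed): from 6 × 0.5 × 0.10 = 0.3 kg to 12 × 1 × 0.10 = 1.2 kg.
- Same attrition, leaver fractions f₁ and f₂: size of bias = dC|f₁ − f₂|. With d = 0.30 and f of 0.5 v 0 (assumed): from 0.30 × 6 × 0.5 = 0.9 kg to 0.30 × 12 × 0.5 = 1.8 kg.

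**Which pre-diet weight.** Under Study design, participants and recruitment, randomisation follows completion of the baseline measurements. Under Data collection, the run-in also follows the baseline assessments, and Week 0 comes at its end. The Week 0 weight may therefore be taken after randomisation; the baseline weight is not.

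**The case against.** The best defence is that the article promises to include all randomised participants. That implies some treatment of a missing Week 12 weight, which could draw on the fortnightly weights. Such detail is commonly left to the full protocol or SAP, which are not shown. Naming an adherence use does not rule out another. A baseline and Week 12 ANCOVA is a standard choice, body weight is secondary, and the overnight fast is stated for outcome assessments only, so interim weights may be noisier.

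Much of this stands, and it rules out several stronger readings:
- A reader might infer that leavers' weights are thrown away. The article does not say so; it names no completers-only analysis, and the weights have an adherence use.
- A reader might infer that weight loss will be overstated. That depends on how leavers fare, for which the documents give no figure.
- A reader might expect a false difference between diets. Nothing in the documents shows that attrition or leavers' loss will differ by arm. Both arms have the same energy restriction, macronutrient targets, counselling and hamper value. Free oil is mentioned for the EVOO arm only, which makes unequal retention conceivable but does not show it.
- A reader might conclude that Week 0 should replace baseline as the starting weight. The order of randomisation and run-in argues against that.

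The defence does not remove the core point. Silence on missing data is not the complaint: the timing of the body-weight outcome and the tests are both stated, and followed as written they leave the interim weights out.

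**Conclusion.** The point holds as a cheap improvement of low severity. The plan fixes body weight at two time points and names two-time-point tests, although it already collects a fortnightly series. With about 22 of 73 expected to leave, that fits poorly with its own commitment to include everyone randomised.

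The 0.9 to 3.6 kg overstatement of mean loss is conditional on three assumptions: that the analysis is confined to Week 12 attenders, that completers reach the 6 to 12 kg target, and that leavers lose no more than half of that. It falls to zero if leavers lose as much as completers. Bias in the comparison of diets needs a further assumption, that attrition or leavers' loss differs by arm. The ASM result is untouched, since weights cannot stand in for missing DXA scans.

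**What to change.** Under Data collection, state that all scheduled weights to Week 12 enter the body-weight analysis. In the statistical section, name a linear mixed model for repeated measures for this outcome, with arm, visit, arm by visit, pre-randomisation baseline weight and BMI stratum, and report the Week 12 contrast between diets. Keep baseline weight as the covariate; Week 0 can enter as a visit, but should not replace it.

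This model lets leaving depend on the weights already observed, a weaker assumption than an analysis of Week 12 attenders needs. It does not cure everything: a participant with no weight after baseline still contributes nothing to the contrast, and bias remains if leaving depends on weights never observed.

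The cost is a change of wording and one model, which the software already named can fit. No visits or measurements are added. The downside is possible extra noise, because fasting is not stated for the fortnightly weighings. Fixing the model in advance also removes a later choice between two analyses of the same outcome.
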